**Vitamin D & Bone Density Testing in**

**VISN 20 Patients with PD**

**Figure 2:** shows how rarely vitamin D and bone density testing are done in men with PD in the VISN 20 system.

**Figure 1:** shows the percentage of men with deficient, insufficient, and sufficient vitamin D levels based on their PD status. Over 70% of men with PD were either deficient or insufficient in vitamin D.

**C.3 Vitamin D levels are correlated with mobility in community dwelling elderly:** Vitamin D levels were correlated with falls, loco-motor function, and cognitive function in subjects from the Intelligent Systems for Assessment of Aging Changes Study (ISAAC). This is a study of adults over age 70 who have computerized equipment in their homes that monitor their movement. They also perform regular computerized questionnaires and come in for periodic testing. Mean vitamin D was 38.0ng/ml (range=9-90 ng/ml). In the 6 months surrounding the vitamin D testing (3 months before and after), 24% (n=37) reported at least one fall. The mean vitamin D of non-fallers was significantly greater 39.7ng/ml (SD 15.3), than both one-time fallers 34.1ng/ml (SD 9.8), and multiple-fallers 28.6ng/ml (SD 11.8) (p=0.03). Vitamin D was also greater in subjects with higher MMSE scores; 42.8±15ng/ml for MMSE=30 (n=42), 36.7±14.4ng/ml for MMSE=27-29 (n=89), and 34.8±13.1ng/ml for MMSE 22-26 (n=21) (p=0.05). Greater plasma vitamin D levels are associated with fewer falls and higher MMSE scores. [name] is responsible for the developing the analysis design in collaboration with a research associate and for the drafting of the abstract and future manuscript. This abstract has been submitted for the 2010 American Academy of Neurology Meeting.

**Figure 4:** shows that the SOT composite score (SOTc) correlated better with performance on UPDRS Postural Response score [normal (0), mildly affected (1) and severely affected (2)] than backwards translation (BT) or sit to stand (S2S).

**Figure 3:** shows the average serum vitamin D levels for non-fallers, single fallers, and multi-fallers. Non-fallers had the highest levels and multi-fallers the lowest.

**C.4 Computerized posturography is sensitive to balance deficits in PD**

C.4.1 Candidate balance tests: Balance testing data itself is important in the design of this study. One of the primary aims of the pilot balance study was to select appropriate balance tests for the intervention study. [name] has enrolled and tested 35 of the 40 subjects planned for the pilot study using 5 posturography tests. The five tests were:

(1)Sensory Organization Test (SOT): The SOT measures sway during 6 scenarios. In 1-3 the base is stable and eyes are open, then closed, and then the visual surround moves. In 4-6 the base moves and the subject has eyes open, then closed, then the visual surround moves. It generates a score of 0 (fall) up to 100 for each scenario and an overall composite score (see D.5.1).

(2)Backwards Translations (BT): Measures latency, symmetry, amplitude scaling, and force of reactions to posterior displacement. The platform upon which the subject stands quickly moves backwards to elicit the reactive response.

(3)Unilateral Stance with Eyes Open and Closed: This test quantifies mean sway velocity and symmetry of standing on one leg with eyes open and closed.

(4)Sit to Stand (S2S): Measures the time to move the center of gravity (COG) over the feet, the amount of force exerted by the legs during the rise phase, the sway velocity (COG sway) and the weight symmetry during the sit to stand task and for 5 seconds after arising.

(5)Walk and Turn: Measures the amount of time to complete a 180 degree turn to the right and then to the left on a narrow platform. It also measures COG during right and left turns.

The balance data on the initial 20 subjects has been analyzed. Several of the tasks were too difficult for the majority of subjects to perform safely (unilateral stance and walk and turn). Subjects consistently performed well on backwards translations and sit to stand; improvements would not be seen with any type of intervention because of a ceiling affect. The SOT stood out as the best test that would be sensitive to changes in balance. Figure 4 shows the relationship between the Unified Parkinson’s Disease Scale (UPDRS) postural response score (also called a pull test) and the 3 posturography tests that the majority of subjects were able to perform (SOT, backwards translation, and sit to stand).

C.4.2 SOT is sensitive to balance impairments in PD: The SOT stood out by far as the most sensitive test of balance impairment in PD. Scores for the SOT range from 0 for a fall to a ceiling of 100, representing perfect stability. Of the various tests used in the pilot study, the SOT is the most widely reported in the literature and has been shown to correlate with falls.^90, 91^ Figure 5 categorizes subjects based on postural response score of the motor UPDRS, showing subjects SOT scores for scenarios 1-6 and the overall composite score. The average

**Figure 5:** shows the 6 SOT scores for PD patients whose UPDRS Postural Response score was normal (0), mildly affected (1) and severely affected (2) during the 6 conditions and composite. The best possible score is 100; a fall is 0.

**Figure 6:** shows the root mean square of velocity in the medial-lateral direction for the 6 SOT scenarios for PD patients whose UPDRS Postural Response score was normal (0), mildly affected (1) and severely affected (2). A lower score corresponds to better balance, falls were rated as 50.

score is higher in the group with normal response on the pull test, with progressively lower scores on SOT as the pull test performance worsens. Another measure that has been shown more sensitive to balance problems in PD, the root mean square of the velocity in the medial lateral direction shows a similar relationship (see Figure 6).^86^

C.4.3 iMOBILITY is sensitive to ambulatory balance deficits in PD: iMOBILITY has not been used in the pilot study. In performing the pilot study [name] realized that one key aspect of balance that was not measured with the battery in the pilot study was ambulatory balance. This is particularly important in PD because of freezing which is only evident when a person ambulates. The walk and turn had the potential to demonstrate ambulatory imbalance but because of the shape and size of the posturography platform used, most of the subjects could not complete the test safely. By adding iMOBILITY, ambulatory balance will be included in the analysis. Although [name] does not have personal experience with this test, [name] and her team have used the device in persons with PD. The specific measure used will be turn duration as measured during a timed up and go using iMOBILITY. Figure 7 from [name] data shows the increase in turn duration time as disease progresses in persons with untreated PD.

**Figure 7:** shows that turn duration increases as PD progresses. Turning takes longer for persons with PD as compared to controls.

**Study Design**

Vit D

level

Not enrolled

Vit D & Ca++ levels

**Baseline**

**Testing**

>40

RANDOMIZE

**High dose vit D & Ca++**

Reassessment

20-40

Reassessment

Placebo & Ca++

High dose vit D & Ca++ (open label)

<20

Reassessment deleted

4 8 12 16

Weeks

**Figure 8:** shows the study design. Starting with baseline testing, randomization based on vitamin D levels, high or placebo dose supplementation, and repeat testing at 16 weeks. Subjects with vitamin D less than 20 ng/ml will be treated in an open-label fashion with high dose supplementation.

Subjects will be recruited from clinics at the Portland VA and OHSU, and from the community. Subjects who agree to participate will come to the Oregon Clinical and Translational Research Institute (OCTRI) on the 10^th^ floor of the Hatfield Research Center at OHSU. Subjects will be consented in one of the exam rooms by the PI, [name]. The study coordinator will then perform the iTUG. Labs will then be drawn across the hall by the OCTRI staff for vitamin D, ionized calcium, phosphate, and creatinine. The Principal Investigator will perform a neurological examination, past medical history, and the MMSE. The subjects will then be walked down to the 8^th^ floor rehab department where a physical therapist or Principal Investigator will perform Parkinson’s disease assessment, dyskinetic and balance assessments. The subjects will tehn be taken down to the Center for Health and Healing (CHH) and have strength testing performed. The subjects will complete a falls diary for the next four weeks prior to enrollment. If the subjects meet inclusion criteria they will be randomized at visit 1a and have further cognitive testing, and complete questionnaires. At visit 1a, subjects will be randomized, falls diary will be distributed and reviewed and the first month of study drug will be dispensed. Visits 2, 3, and 4 will also take place at OCTRI (either in the main hospital or at CHH dependent on subject and provider preference). Again they will have blood drawn for vitamin D, ionized calcium, phosphate, and creatinine. At visits 2, 3, and 4 pill counts will be done, falls diaries reviewed, the next 4 weeks of medications given, and labs repeated. [name] will review the labs after each visit and inform the study coordinator if any patients need to be removed from the study. The 5^th^ and final study visit is similar to the first visit and will take place at OCTRI in the main hospital, the rehab department on the 8^th^ floor of the main hospital building, and balance testing in rehab at CHH. Subjects will undergo the full battery of PD severity, medical history, cognitive, depression, quality of life, laboratory, balance, dyskinesia, and strength testing. Patients will be asked to keep falls diary for the 8 weeks following the study and mail them in. They will be contacted by phone 8 weeks after completion and asked about any subsequent potential side effects from the intervention during the study.

**D.2 Study Population**

Inclusion Criteria: (1) Medically confirmed diagnosis of PD by a movement disorders specialist using the National Institute of Neurological disorders and Stroke (NINDS) criteria. (2) Ability to ambulate 50 feet without the assistance of another person. (3) Ability to cooperate with balance testing. (4) 50 + years of age. (5) Vitamin D level between 20 ng/ml and 40ng/ml. (6) Some degree of balance dysfunction indicated by: a score of 1 or greater on the pull test or 1 fall in last month or 2 near falls in the last month.

We have chosen to focus on person with at least some minor balance problems, a medical history of at least two near falls within the last month or some degree of balance dysfunction as measured by the pull test score of ≥ 1. People with very severe balance deficits would not be able to complete testing so subjects need to be able to walk at least 50 feet without the assistance of another person. We have chosen persons with insufficiency and low sufficient levels of vitamin D assuming that persons with lower levels will respond more robustly to supplementation, as has been seen in other studies.

Exclusion Criteria: (1) Significant cognitive deficits as defined by a Mini Mental Status Exam (MMSE) of <25. (2) Another neurological or orthopedic deficit that in the investigator’s opinion would have a significant impact on gait and cognition (e.g. stroke, fracture). (3) History of renal stones or renal disease (history of renal transplant, currently on dialysis, or a creatinine > 1.5 at baseline testing). (4) Subjects cannot be on > 600 IU vitamin D supplementation during the study. (5) Hypercalcaemia (based on ionized calcium level). (6) Known tuberculosis infection who have not been treated. (7) Pregnancy. (8) Soy Allergy.

For safety we will exclude anyone with hypercalcaemia(or a history of this), a history of kidney stones, renal disease, or untreated tuberculosis as the risk of the risk of hypercalcaemia and stones are increased with supplementation in these particular populations. Since we are using a fairly high dose for the vitamin D arm, we have also added the additional measures of phosphate and creatinine. As some other medical conditions such as a severe stroke or major orthopedic problem could affect testing, the PI will have discretion to not enroll such persons. We did not want to have frankly demented patients as cognitive testing could affect ability to cooperate with testing.

**Table 4: Detailed time line**

| **Year of grant (date)** | **Activities** | **# of subjects completed** |
| --- | --- | --- |
| 1 (July 2010-2011) | IRB approval  Animal research project  Recruitment  Begin data collection | 40 |
| 2 (July2011-2012) | Data collection | 80 |
| 3 (July 2012-2013) | Data collection | 120 |
| 4 (July 2013-2014) | Data collection  Analysis of baseline data | 140 |
| 5 (July 2014-2015) | Data analysis  Manuscript Preparation | 140 |

Randomization: We will use a permuted block randomization scheme to allocate treatments using strata determined by two factors: baseline vitamin D levels (>20-<30 vs. >30-<40ng/ml) and baseline composite SOT4-6 ( <64 vs. >64). This is based on what is considered insufficiency of vitamin D and the mean normative SOT score for persons 70-79 years old respectively.^59, 92^ Those with < 20 ng/ml baseline vitamin D levels will be enrolled into the vitamin D supplementation arm and will receive 10,000 IU of vitamin D for 16 weeks in an open label fashion. Those with > 40 ng/ml at baseline will not be enrolled in this study.

**D.3 Study Procedures**

D.3.1 Balance Measures: To limit variability in PD symptoms and medication effects throughout the day assessments will occur at the same time for each individual subject. This will be approximately half way between PD medication doses to attempt to get subjects in the “on” state. This is when most falls occur and how most patients try to spend the majority of their waking hours. The primary outcome measure will be a composite score of static and dynamic balance, as measured by the SOT composite score using dynamic posturography (see D.5.1). SOT composite includes 6 scenarios that replicate daily activities that often lead to falls. As shown by our preliminary data it is sensitive to balance problems seen in PD and has been shown to correlate with falls in other populations.^90^ The SOT was chosen from a much larger array of balance tests available based on the pilot study data (see C.4.1). Subjects performed moderately on this test such that there should not be a ceiling affect (where improvement could not be seen) or a floor affect (where subjects perform so poorly that even modest improvement would not be detectable). In addition if the SOT composite is not sensitive to balance changes we will calculate the root mean square velocity in the medial lateral direction (see C.4.2). Turning duration is also included for an ambulatory balance measure. Freezing of gait is a major cause of falls in PD and would not be evident with the SOT.^25^ This also has been shown sensitive to balance problems in PD and able to detecting balance problems early in PD when traditional testing in negative.^30^ This will be recorded using the iMOBILITY device and an instrumented timed up and go test (see D.5.2).

**Table 5: Time Table and Organizational Chart**

| Prior to study visits: | | Identification of potential subjects | | |
| --- | --- | --- | --- | --- |
| **Study Visit 1**  Screening Visit  Main Hospital  (120 minutes) | Review of inclusion & exclusion criteria  Consent  (5 minutes) | **Measures:**  (75 minutes)  Balance: SOT,MCT, iTUG | **Laboratory:**  (15 minutes)  Vitamin D  Ionized Ca^++^  Phos  Creatinine  Serum beta hCG | **Possible Confounder:**  (30 minutes)  Medication list  Cognitive tests (MMSE)  PD severity(UPRDS)  Dyskinesia |
| **Study Visit 1 a**  Enrollment  CHH  (90 minutes) | Randomization | **Measures:**  (20 minutes)  Strength: Biodex  QOL: PDQ39, NHP, ABC, POMS, Falls diary review |  | **Possible Confounder:**  (70 minutes)  Other cognitive testing  Medication List |
| **Study Visits**  **2-4**  Main Hospital or CHH  (30 minutes) | Review of lab inclusion & exclusion criteria | **Measures:**  (15 minutes)  Falls diary review  Pill count | **Laboratory:**  (15 minutes)  Vitamin D  Ionized Ca^++^  Phos  Creatinine | Distribution of Study Drugs |
| **After Visits 2-4** | Review of laboratory data | Telephone contact with patient and withdraw from study if elevated vitamin D, Ca^++^, Phos, creatinine | | |
| **Study Visit 5**  Main Hospital and CHH  (150 minutes) |  | **Measures:**  (75 minutes)  Balance: SOT, MCT, iTUG  Strength: Biodex  QOL: PDQ39, NHP, ABC, POMS | **Laboratory:**  (15 minutes)  Vitamin D  Ionized Ca^++^  Phos  Creatinine | **Possible Confounder:**  (30 minutes)  Medication list  Cognitive tests  PD severity(UPDRS)  Dyskinesia |
| **Phone Call**  **(10 minutes)** | Review of any potential adverse events | **Falls diary (mailed)** |  |  |

**D.3.2 Strength measures**

The frequency that a person falls is known to be affected by muscle strength.^93^ Severe vitamin D deficiency can cause myopathy and studies show that vitamin D supplementation improves muscle strength.^61^ In the proposed studies we will measure strength of leg flexion and extension. These are the major muscles involved in gait and are fairly easy to test using the Biodex system. We chose Biodex computerized dynamometer testing because this allows for more sensitive and consistent data then hand held dynamometers and can calculate total work as well as peak torque, a better measure of muscle function.^94^ We will use total work in the analysis. The baseline data in and of itself will be of interest as there is little data about strength changes in persons with PD.^95, 96^

**D.3.3 Quality of Life Measures**

Because falls and mobility issues play a major role in quality of life for persons with PD we expect to see these measures improve if there is a clinically meaningful change in balance.^17, 97^ We chose 2 scales, the NHP being a general QOL measure and the PDQ-39 a PD specific scale.^98, 99^ Study participants will be asked to complete the NHP and the PDQ-39 at visits 1 and 5. Both questionnaires generate a score of 0 to 100. The NHP asks 38 yes or no questions in categories of emotional reactions, sleep, energy, pain, physical mobility, and social isolation. The PDQ-39 has 39 items in categories of mobility, activities of daily living, emotional well-being, stigma, social support, cognitions, communication, and bodily discomfort. Both scales have been validated for use in PD.^99^ Because fear of falling also results in limitation we will perform the 16 item Activities-specific Balance Confidence (ABC) Scale at visits 1 and 5.^15^ The ABC scale questions percent confidence (0-100%) subjects have for not losing their balance during a variety of activities. Depression will be measured using the profile of Mood States (POMS) questionnaire, a 30-item mood questionnaire.

**D.3.4 Intervention**

Subjects will be assigned to one of two groups: (1) placebo plus 1000 mg calcium or (2) 10,000 IU vitamin D up to a maximum of 15,000 IU plus 1000 mg calcium once daily for 5 days each week. Vitamin D, calcium, phosphate, and creatinine levels will be checked every 4 weeks to be sure patients’ levels are not too high. With new locations and functions of vitamin D being discovered definition of sufficient and insufficient levels are in question. The recommended daily allowance (RDA) of vitamin D for persons 51-70 years old is 400 IU and for those over 71 years old is 600 IU.^100^ We have chosen a fairly aggressive supplementation with the rational that in a short term study getting higher levels sooner would increase the chance of seeing a change. Since the study is of such short duration and we are not including persons with clear deficiency we feel a true placebo arm is justified and will make the study stronger.

A weekly dose of 50,000 IU to 75,000 IU is felt to be a safe dosage. Other studies are approved using levels over 7,000 IU a day for an entire year. Data is limited in humans but levels consistently above 200ng/ml are considered potentially toxic.^62^ Even the 200ng/ml level may be safe and more in-depth animal studies have not indicated toxicity in levels under 400ng/ml.^101^ We will check levels monthly and for the utmost safety, subjects will be removed from the study if their levels are above 100ng/ml. In addition since the most common problem with vitamin D supplementation is hypercalcaemia, we will check monthly ionized calcium as well as phosphate, and creatinine for added safety.

The vitamin D will be obtained from Capsugel and the calcium carbonate directly from the VA pharmacy (BTR Group Inc is source). The regiments are detailed in the table below. Each subject will take pill 5 days a week (Monday thru Friday).. The vitamin D placebo is also manufactured by Capsugel and has an identical appearance to the active capsule . Both will be provided in bottles to assist with compliance and ease of administration and pill counting.

**Table 6: Medication Regiment for Placebo and High Dose Groups**

| **Placebo Group (M-F)** | **High Dose Group (M-F)** |
| --- | --- |
| 2-Calcium 500mg  1-Placebo (blinded) | 2-Calcium 500mg  1 Vitamin D3 10,000 IU up to a maximum of 15,000 IU (blinded) |

**D.3.5 Falls Assessment**

Subjects will be given a diary in which to record their falls at visit 1. They will be instructed to write the time of day of the fall, what they were doing when they fell, if they sustained an injury, and classify it as a fall or near fall. Falls will be defined to subjects as unintentionally coming to rest on the ground, or another lower level such as a chair, toilet, or bed.^102^ A near-fall will be defined as a slip (sliding of the support leg), trip (impact of the swinging leg with an external object) or loss of balance where the person starts to fall but is able to stop or prevent the fall to the ground or other lower surface.^103^ Subjects will be asked in person every 4 weeks when they meet with the study coordinator how often they fell and the diary will be reviewed. They will also be asked to keep a falls diary for the 8 weeks after study completion and return these by mail. Even though the study is not powered for falls and 16 weeks is a very short period to measure changes in fall frequency we felt it was important to collect this data.

**D.3.6 Monthly Labs**

In addition to the baseline measures, blood will be drawn every 4 weeks to serum check 25-hydroxyvitamin D (25-OHD), ionized calcium, phosphate, and creatinine after supplementation is begun. This is more extensive and frequent testing than generally done with supplementation, but because of the high dose arm we want to ensure absolute safety. Labs will be reviewed by [name]. If a marked elevation or decrease of vitamin D levels (>100 ng/ml), ionized calcium (>1.32 mmol/L), phosphate (> 5.5 mg/dL), or creatinine (>30% change) are found, the subjects will perform the final study visit and will discontinue in the study. This is a safety measure and not part of the inclusion/exclusion criteria. 15 mL of blood from the screening visit and the final visit will be banked in a VA approved bio-repository.

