**D.4.0 Statistical Analysis**

D.4.1 Sample Size: We are basing our power calculation on the primary outcome, the composite SOT (cSOT) score from computerized posturography, for Aim 1. Although we are not assessing power for other outcomes, we will have a reasonable amount of data, targeting 70 subjects per group, to obtain useful information about additional outcomes. Using preliminary data on 20 subjects (see C.4), the average cSOT (SD), excluding one score of zero, was 58.5 (19.1). For conducting a power calculation on the cSOT measure we assume that 10% of subjects will score zero at baseline and follow-up. This is conservative since only 5% of the 20 subjects used for our preliminary data scored zero at a single time point. Among the remaining subjects, we assume SD’s of 19.1 at baseline and follow-up, that the high dose group will have an average score that is 8.8 points higher than at baseline (15% change from 58.5) and the placebo group shows no improvement. There are not studies looking at changes in SOT with vitamin D supplementation, but the Pfeifer did look at body sway, finding a 15% greater improvement in body sway in the intervention versus the control group.^111^  With 10% zeros this 15% change among the non-zeros translates to a mean difference in change of 7.9 points. The SD of the changes from baseline depends on the SD’s at baseline and follow-up and on the correlation between baseline and follow-up measures. We hence obtained sample size requirements using a range of correlation coefficients.

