Using simulation with PASS 2008 software, we determined (see Table 7), the sample sizes needed to detect the 7.9 point mean difference indicated above with 80% power at significance level 0.049 (allowing for an interim analysis at significance level .001) for correlations between 0.5 and 0.75. The simulation method was based on the Mann-Whitney nonparametric test which is more conservative in this setting than a t-test procedure (that is, using a simple t-test for the simulation would result in smaller required sample sizes). We will adjust for confounders using parametric methods, but used the non-parametric approach for sample size selection to assure that enough subjects are selected for simple comparisons. The Balance Manager Systems Clinical Interpretation Guide for Computerized Dynamic Posturography report test-retest reliability results ranging from 0.66 to 0.98 for the cSOT.^92^ With 0.66 for correlation, we would require 63 subjects per group. Allowing for 10% drop-out we will then plan to recruit 70 subjects per group.

**Table 7. Sample sizes per group needed for 80% power at significance level 0.049 to detect a mean difference in posturography composite change of 7.9.**

| SD at baseline and at follow-up for composite posturography | Correlation between baseline and follow-up composite posturography | SD of difference between follow-up and baseline scores | Sample size per group |
| --- | --- | --- | --- |
| 19.1 | 0.50 | 19.1 | 91 |
| 19.1 | 0.66 | 15.8 | 63 |
| 19.1 | 0.75 | 13.5 | 47 |

D.4.2 Interim Analysis: When half of the targeted subjects have completed the follow-up visit, we will conduct an interim analysis of the primary outcome using a significance level of 0.001. This was felt appropriate to ensure additional safety for patients. The primary outcome analysis and analysis of other outcomes will be presented to the Data Safety Monitoring Committee, which will be made up of a group of researchers not directly involved in this project. Using a small significance level for the interim analysis requires strong evidence of an effect of Vitamin D for consideration of early stopping (We will use a significance level of 0.049 for the final analysis so that the Type I error rate for the primary outcome remains controlled at 0.05.). The details of the methods used at the interim and/or final analyses are described below.

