**D.6 Possible Pitfalls:**

Recruitment is not expected to be an impediment. Our center is historically very successful in recruiting patients and the inclusion criteria here are quite broad. With a study coordinator involved the pilot study enrolled 8-10 subjects a month, with many more expressing interest. Retention of subjects for 16 weeks in study of a treatment (high dose vitamin D) which is available outside of the study may be challenging. We will also provide $10 per visit and the statistical analysis plan accounts for a drop-out rate of 10%. There are other sources of vitamin D including sun exposure and diet. By choosing a fairly high dose for the intervention group dietary and sun sources are likely to be minimal in comparison. In addition by measuring plasma vitamin D levels we can identify subjects who “drop in” with surreptitious or inadvertent use of vitamin D supplements, dietary changes, or changes in sun exposure related to season. Eight or 12 weeks may be an insufficient treatment period over which to see a treatment effect—this is precisely why outcomes are measured at 16 weeks.

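### Subjects who cross a lab limit get no week-16 balance test, and the vitamin D limit will in practice select them from one arm

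*Protocol*

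**What the plan says.** Vitamin D, ionized calcium, phosphate and creatinine are measured every four weeks. D.3.6 sets a limit for each (vitamin D above 100 ng/ml, ionized calcium above 1.32 mmol/L, phosphate above 5.5 mg/dL, creatinine change over 30%). When one is crossed, "the subjects will perform the final study visit and will discontinue in the study". The section describes this as a safety measure.

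Other sections describe the same event without a final visit:

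- D.3.4: "subjects will be removed from the study if their levels are above 100ng/ml".
- Table 5, in the row for the period after Visits 2-4: "Telephone contact with patient and withdraw from study if elevated vitamin D", with the other three labs listed after it.
- D.1, in the visit description: the person reviewing the labs is to "inform the study coordinator if any patients need to be removed from the study". E.5 repeats this in similar terms.

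D.1 places repeat balance testing at 16 weeks. D.6 explains the timing: "Eight or 12 weeks may be an insufficient treatment period over which to see a treatment effect". The primary analysis (D.4.3.1) is a Mann-Whitney test on change in composite SOT. The same section plans a sensitivity analysis if drop-out is more than negligible and accepts that selective drop-out would bias the conclusions.

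**The concern.** Stopping capsules and ending outcome follow-up are different decisions, and the protocol joins them. Whether a subject has a week-16 outcome then depends on a lab value that is itself affected by treatment. Randomised subjects start at 20-40 ng/ml and only one arm receives vitamin D, so the limit of 100 ng/ml acts in practice on the vitamin D arm and on the subjects with the greatest serum response. For them the comparison would use a balance score taken earlier than the protocol thinks adequate, or, if staff follow Table 5 or D.3.4 literally, perhaps no score.

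At stake are the randomised week-16 comparison and its power. If no outcome is taken, the planned secondary analysis of balance change against serum change also loses the upper end of its exposure range. An analysis plan can say how to handle a missing week-16 value, but it cannot recover a test that was never done.

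**Working it through.** **Reading the sections together.** Draws that can trigger an early exit are those at Visits 2, 3 and 4, that is weeks 4, 8 and 12. D.3.6 yields an early composite SOT. D.1, D.3.4, Table 5 and E.5 neither require nor exclude one. None of the five brings the subject back at week 16.

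**Inputs (D.4.1 and Table 7).**

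- Design level: "80% power at significance level 0.049 (allowing for an interim analysis at significance level .001" and so on; two-sided is assumed, since it reproduces the stated size. The critical value is z = 1.969.
- Effect among non-zero scorers: "the high dose group will have an average score that is 8.8 points higher than at baseline", with no change on placebo. With 10% zeros this "translates to a mean difference in change of 7.9 points": 0.9 × 8.8 = 7.92.
- SD of change at correlation 0.66: 19.1 × √(2 × (1 − 0.66)) = 15.75.
- 63 evaluable per arm, 70 recruited.
- Share of the vitamin D arm that exits, f: not in the protocol. I assume 10%, 20% and 30%.

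**Reproducing the plan.** n = 2 × (1.969 + 0.842)² × 15.75² / 7.9² = 62.8, so 63 per arm. 63 / 0.9 = 70. A Mann-Whitney simulation (20,000 runs, 10% zero changes, other changes normal with SD 15.75 and mean 8.8 or 0) gives about 80% power at 63. The sample-size arithmetic is sound.

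**Early values used as the outcome.** If an early value carries a fraction e of the 16-week effect, the mean difference is d = 7.9 × (1 − f(1 − e)) and power is Φ(d / 15.75 × √(63/2) − 1.969). With f = 0, this is Φ(2.815 − 1.969) = 80%.

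| Exits in vitamin D arm | e = 0.5: difference | e = 0.5: power, formula / simulation | e = 0: difference | e = 0: power, formula / simulation |
|---|---|---|---|---|
| 10% | 7.5 | 76% / 77% | 7.1 | 71% / 72% |
| 20% | 7.1 | 71% / 71% | 6.3 | 61% / 60% |
| 30% | 6.7 | 66% / 67% | 5.5 | 50% / 49% |

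**No value taken (simulation, exits taken out of 63).**

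- Exit unrelated to response: power 78%, 75% and 73% at 10%, 20% and 30%, with no bias.
- Those who exit would have had 1.5 times the average effect: power 74%, 64% and 52%, with the mean difference reduced to 7.5, 6.9 and 6.2.

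**What the drop-out allowance covers.** If 10% of the vitamin D arm exits without data and nobody else drops out, 63 and 70 subjects remain. The standard error is 15.75 × √(1/63 + 1/70) = 2.735, and power is Φ(7.9 / 2.735 − 1.969) = 82%. The allowance restores numbers at that rate. It does nothing about who is missing.

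**The case against.** The sections may be one rule told at different lengths. D.3.6 is the fullest text, and none of the shorter statements says that the final visit is skipped. This largely stands. A reader might infer that the highest-exposed subjects vanish from the comparison, but under D.3.6 they have an early composite SOT. That no outcome is taken is only a possibility, left open by silence elsewhere.

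A reader might also infer that all lab exits come from one arm. The protocol does not support that. Both arms take 1000 mg calcium, and the calcium, phosphate and creatinine limits can be crossed on placebo. The one-sided argument rests on the vitamin D limit alone.

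It is tempting, too, to see unblinding, because D.1 has the coordinator both perform the iTUG and hear of removals. D.1 and E.5 do not say that the coordinator learns the reason, three of the four reasons do not point to an arm, and the iTUG is not the primary outcome. I make no such claim.

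D.4.3.1 plans a drop-out sensitivity analysis and D.4.1 allows 10% drop-out. Both are real safeguards. The analysis is conditional, however, does not mention lab exits, and leaves unclear whether an early final visit counts as drop-out.

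Finally, zero effect at an early visit is a harsh assumption. D.6 says only that 8 or 12 weeks may be too short, and B.2 cites improved body sway after 8 weeks. That stands, and it is why the zero-effect column is an extreme and not an expectation.

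**Conclusion.** The point holds. For subjects who cross a lab limit, the protocol gives no route to a week-16 composite SOT, and its sections need reconciling on how these subjects leave. Because the vitamin D limit will in practice be met only on active treatment, the affected group is selected after randomisation and weighted to one arm.

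The size cannot be fixed from the protocol. With 10% to 30% of the vitamin D arm exiting, power is about 77% to 67% if early values keep half the effect and about 71% to 50% if they keep none. With few exits the loss is small. If the values are missing but unrelated to response, there is some loss of power and no bias. The figure of 50% should not be read as a forecast: it needs both a 30% exit rate, for which the protocol gives no basis, and no effect at all at the early visit.

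The case for changing the text rests less on these figures than on the fact that missing week-16 tests cannot be recovered later and cost little to collect.

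**What to change.** Reconcile D.1, D.3.4, D.3.6, Table 5 and E.5 so that they describe one procedure. Leave the lab limits, the decision to stop and any safety assessment at exit to the clinicians as they stand. Then add three statements:

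1. Ending study capsules does not end follow-up.
2. The Visit 5 balance and strength tests are sought at week 16 from every randomised subject who agrees, on or off capsules.
3. The primary analysis compares subjects as randomised, using the week-16 value. An early exit measurement, where taken, is recorded but does not replace it.

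The cost is protocol wording and possibly a second testing visit for a few subjects; Table 5 puts the full Visit 5 at 150 minutes. For subjects who stop early, the week-16 value includes time off capsules, so some dilution of the effect is accepted in return for keeping the randomised comparison intact.
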